## Abstract

**Background:**

Patients with end stage liver disease are characteristically malnourished which is associated with poor outcome. Formulas enriched with arginine, ω-3 fatty acids, and nucleotides, "immunonutrients", potentially improve their nutritional status. This study is designed to evaluate the clinical outcome of long-term "immunonutrition" of patients with end-stage liver disease while on the waiting list for liver transplantation.

**Methods/design:**

A randomized controlled double blind multi-center clinical trial with two parallel groups comprising a total of 142 newly registered patients for primary liver transplantation has been designed to assess the safety and efficacy of the long-term administration of ORAL IMPACT^®^, an "immunonutrient" formula, while waiting for a graft. Patients will be enrolled the day of registration on the waiting list for liver transplantation. Study ends on the day of transplantation. Primary endpoints include improved patients' nutritional and physiological status, as measured by mid-arm muscle area, triceps skin fold thickness, grip strength, and fatigue score, as well as patients' health related quality of life. Furthermore, patients will be followed for 12 postoperative weeks to evaluate anabolic recovery after transplantation as shown by reduced post-transplant mechanical ventilation, hospital stay, wound healing, infectious morbidities (pneumonia, intraabdominal abscess, sepsis, line sepsis, wound infection, and urinary tract infection), acute and chronic rejection, and mortality.

**Discussion:**

Formulas enriched with arginine, ω-3 fatty acids, and nucleotides have been proven to be beneficial in reducing postoperative infectious complications and length of hospital stay among the patients undergoing elective gastrointestinal surgery. Possible mechanisms include downregulation of the inflammatory responses to surgery and immune modulation rather than a sole nutritional effect.

**Trial registration:**

ClinicalTrials.gov NCT00495859

## Background

### Immunonutrition

Patients with end-stage liver disease (ESLD) characteristically suffer from protein-energy malnutrition (PEM) and hypermetabolism due to abnormal nutrient and caloric intake, decreased intestinal absorption, and metabolic disturbances, which is associated with poor outcome including poor perceived health-related quality of life (HRQL) [1,2] and unsatisfactory postoperative course, i.e., prolonged intensive care unit and total hospital stay, prolonged mechanical ventilation, and increased morbidities and mortality [3,4]. The biochemical nutritional derangements include deficiency in ω-3 and ω-6 long-chain fatty acids [5], insulin resistance [6], growth hormone resistance [7,8], increased proinflammatory cytokines (e.g., TNF-α, IL-1, IL-6) [9], and increased lipid peroxidation due to a deficiency in endogenous antioxidants, i.e. vitamin E and carotenoids [10,11], all of which lead to a clinical manifestation of progressive lipolysis and proteolysis. Supplementation with ω-3 fatty acids may downregulate proinflammatory cytokine production and modulate eicosanoid synthesis [12-14]. The latter molecules lead to the production of vasodilators, i.e. LTB5, PGE3, PGI3, and TxA3, thus acting against inflammation, aggregation, adhesion, and chemotaxis [15]. Arginine, which cannot be produced in catabolic states, stimulates the release of anabolic hormones (growth hormone, insulin), improves nitrogen balance and wound healing, upregulates immune function, and enhances NO biosynthesis [16-18]. An increase in protein synthesis can be achieved with nucleotides [19]. Nucleotides can also enhance a variety of host defense mechanisms [20]. Formulas enriched with arginine, ω-3 fatty acids, and nucleotides (immune enhancing diets or the so-called "immunonutrients" – which are designed to modulate a patient's immune response and can hence augment basic nutritional repletion) have been proven to be beneficial in reducing postoperative infectious complications and length of hospital stay among the patients undergoing elective gastrointestinal surgery, especially in those who are malnourished preoperatively [21]. Possible mechanisms include downregulation of the inflammatory responses to surgery and immune modulation rather than a sole nutritional effect.

### Trial Rationale

The interval between listing and transplantation, which may usually extend to several months, provides a unique opportunity for the physician to institute a nutritional therapy. However, clinical studies concerning the long-term preoperative supplementation with such immune-modulating formulas in the field of transplant surgery are rare and inconclusive. Up to 30 papers between 1995 and 2005 under the topic of "immunonutrition and surgery" were found in the literature and reviewed. However, none investigated the long-term preoperative outcome of such supplementation (all just covered a short-term peri- or postoperative period), and few, if any, directly considered the liver transplant patients. Concerning the supplementation of the patients in the waiting list for transplantation, 4 studies were found in the literature, of which only one was randomized. The latter trial investigated the preoperative nutritional supplementation in patients awaiting elective orthotopic liver transplantation (LT) and was designed to determine whether nutritional supplementation improves nutritional status and affects outcome after transplantation. However, it failed to reveal any significant effect on outcome after transplantation, although it improved some parameters of nutritional status pretransplantation. The investigators didn't use any immune-enhancing diet in the trial [22].

Preliminary results of a recent nonrandomized pilot study suggest that immunonutrition may improve short-term preoperative nutritional status, hasten recovery after transplantation, and reduce postoperative infectious complications [23]. Preoperative feeding was started after patients got to the top of the waiting list (and was continued for at least 5 days posttransplant). ORAL IMPACT^® ^(Novartis Consumer Health, Nyon, Switzerland) was used with no adverse short-term consequences.

Therefore, this study is unique because it is randomized and it fully investigates the effects of ORAL IMPACT^® ^during a long-term period in patients waiting for a LT. In this manner, the comparison between patients receiving ORAL IMPACT^® ^(arginine/ω-3 fatty acids/nucleotide enriched formula) or an isocaloric isonitrogenous control may help to identify the exact role of immunonutrition in patients with ESLD.

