## Methods/Design

### Subject recruitment

After the positive vote of the ethics committee of the Faculty of Medicine, Ruprecht-Karls University of Heidelberg, enrollment of 142 newly registered patients for primary LT will be started early in September 2007 in this prospective multicenter placebo-controlled randomized double-blind clinical trial with two parallel treatment groups receiving either study product or control supplement. Patients are considered for recruitment to the study according to inclusion and exclusion criteria (Table 1). Each subject is expected to be recruited on the day of registration on the waiting list for LT. Study nutrition ends on the day of transplantation. To assess early outcome after transplantation patients are followed for 12 postoperative weeks. The duration of the overall trial is expected to last approximately 36 months. The actual duration of trial may vary due to the availability of patients meeting the criteria after registration for LT.

**Table 1 T1:** Criteria for inclusion and exclusion of patients.

**Inclusion criteria**	**Exclusion criteria**
patients meeting all of the following criteria are considered for inclusion in the study: - men and women, 18–68 years of age - scheduled for first liver transplantation - written informed consent - protein-calorie malnutrition defined as mid-arm muscle area (MAMA) <85% standard	patients with any of the following will not be included in the trial: - patients <18 and >68 years - pregnant or nursing women - history of hypersensitivity to arginine, ω-3 fatty acids, or nucleotides - inability to take oral nutrition - patients with fulminant or subacute hepatic failure - mental condition rendering the subject incapable of understanding the nature, scope, and consequences of the trial No subject will be enrolled in this study more than once.

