### Trial design and schedule (Fig. 1)

**Figure 1 F1:**
[figure not shown]
**Scheme depicting the workflow of the study**. Each subject will be recruited on the day of registration on the waiting list for liver transplantation after giving informed consent. Study nutrition ends on the day of transplantation. Subjects are randomized to two parallel groups treated for study or control product. Furthermore, patients will be followed for 12 weeks after transplantation.

Site number, patients' randomization number and initials, all demographic data (date of birth, sex, height, weight), medical history (including a complete dietary history and MELD score), physical examination, comorbidities, and concomitant medications are documented on day one. Furthermore, anthropometric, physiologic, and biochemical measurements are carried out and documented. The aforementioned measurements are performed during monthly visits until transplantation. The patients consume either the study product (ORAL IMPACT^®^) (Table 2) or control product (IMPACT-control supplement) (Table 2) once a day for the period of waiting until a graft is available. During each visit, the following data are recorded in the electronic case report form (eCRF):

**Table 2 T2:** Composition of ORAL IMPACT^® †^and IMPACT Control supplement (in powder form)

Content (1 Sachet)		**ORAL IMPACT^® ^**(74 g)	**IMPACT Control **(74 g)
-Protein	g	16.7	13.0
-Casein/Whey	g	(13)	(13)
-L Arginine	g	(3.74)	-
-Fat	g	8.3	8.3
-Essential FA (LA+LNA)	g	(0.94)	(2.6)
-n-6-FA (LA)	g	(0.74)	(2.6)
-n-3FA (EPA+DHA+LNA)	g	(1)	-
Carbohydrates	g	40.2	43.94
Fibres	g	3	3
RNA	mg	390	-
Energy	g	302.8	302.8
-kcal/ml		§	§
-P:F:C	%	22:25:53	17:25:58
Sodium	mg	320	320
Potassium	mg	402	402
Calcium	mg	240	240
Magnesium	mg	80	80
Phosphorus	mg	216	216
Chloride	mg	480	480
Iron	mg	3.6	3.6
Copper	mg	0.5	0.5
Manganese	mg	0.6	0.6
Zinc	mg	4.5	4.5
Fluoride	mg	0.5	0.5
Iodine	mcg	45	45
Chromium	mcg	30	30
Molybdenum	mcg	60	60
Selenium	mcg	14	14
Retinol (Vit. A.)	mg	0.3	0.3
Calciferol (Vit. D)	mcg	2	2
Tocopherol (Vit. E)	mg	4	4
Phyllochin. (Vit. K1)	mg	20	20
Thiamine (Vit. B1)	mg	0.36	0.36
Riboflavine (Vit. B2)	mg	0.52	0.52
Pyridoxine (Vit. B6)	mg	0.44	0.44
Cyanocobal. (Vit. B12)	mcg	1.2	1.2
Ascorbic Acid (Vit. C)	mg	20	20
Biotin	mcg	30	30
Folic Acid	mcg	60	60
Niacinamide	mg	4.8	4.8
Pantothenic Acid	mg	2.4	2.4

^†^; IMPACT^® ^is a food for special medical purpose (FSMP)

§ content of sachet to be dissolved in 250 ml water for each serving

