In order to establish a nutritional support, an ideal product is what has undergone an extensive evaluation for safety and efficacy through prospective randomized clinical trials. Considerable evidence supports that IMPACT^® ^specialized nutrition support positively influences inflammatory, metabolic, and immune responses to major surgery [45]. However, any nutrient that can alter immune function deserves critical evaluation for potential adverse effects. Up to now, no adverse effects has been reported in patients supplemented with IMPACT^® ^[45]. Concerning the L-Arginine content of IMPACT^® ^and its use in patients with ESLD, a recent pilot study on fifteen patients with ESLD receiving two 74 g sachets of ORAL IMPACT^® ^(each containing 3.74 g L-Arginine) daily (twice as much as the daily administered amount in current study) for a median of 54 (range 10–168) days pre-transplant showed no adverse consequences that could be attributed to the nutritional product [23]. Furthermore, the total protein content of IMPACT^® ^is 16 g, which is far below the 1.2 g/kg daily protein requirement of the patients with ESLD [29].

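### The control is called isonitrogenous, but Table 2 shows it is isocaloric only, so a MAMA difference cannot separate immune modulation from extra amino-acid nitrogen

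*Protocol article*

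**What the plan says.** The protocol article, Background, Trial Rationale, describes the comparator in the sentence that justifies the trial: comparison with "an isocaloric isonitrogenous control may help to identify the exact role of immunonutrition in patients with ESLD".

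Table 2 gives the composition of one sachet, with ORAL IMPACT first and the control second:

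- protein: "Protein g 16.7 13.0"
- casein/whey: 13 g in each
- L-arginine: 3.74 g in ORAL IMPACT, none in the control
- carbohydrate: "Carbohydrates g 40.2 43.94"
- fat: 8.3 g in each
- RNA: 390 mg in ORAL IMPACT, none in the control
- energy: 302.8 in each (the row is labelled g, but kcal is evidently meant)
- percentage of energy from protein, fat and carbohydrate: "22:25:53 17:25:58"

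The Discussion repeats the arginine content of the sachets ("each containing 3.74 g L-Arginine").

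Three other places bear on the interpretation. The Immunonutrition section defines immunonutrients as arginine, ω-3 fatty acids and nucleotides, and lists better nitrogen balance among arginine's actions. It also suggests that the benefit seen in surgical patients comes from immune modulation and not from nutrition alone. The Conclusion makes immune modulation the working hypothesis. The Sample size calculation rests on MAMA.

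**The concern.** In this rationale, isonitrogenous describes the feature that would let a reader set aside the plain nutritional explanation. If both arms received the same energy and the same nitrogen, better preservation of muscle under ORAL IMPACT would be hard to put down to more amino-acid nitrogen. Something specific to the immunonutrients would be the likelier explanation. If nitrogen is not matched, that inference is lost.

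The point matters more here than in a trial with an infection endpoint. MAMA is a muscle measure, it is the endpoint on which the trial is sized, and Table 1 admits only patients whose MAMA is below 85% of standard. Extra nitrogen is a natural rival explanation in such patients. A reader who trusts the Trial Rationale would believe that the design had ruled it out.

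**Working it through.** **1. Is Table 2 internally consistent?** All inputs are from Table 2.

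- Protein, ORAL IMPACT: 13 (casein/whey) + 3.74 (arginine) = 16.74 g, printed as 16.7 g. Arginine is the whole protein gap.
- Protein, control: 13 g casein/whey, printed as 13.0 g.
- Carbohydrate: 43.94 − 40.2 = 3.74 g. The control replaces arginine gram for gram with carbohydrate, not with another nitrogen source.

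**2. Does isocaloric hold?** Energy = 4 × protein + 9 × fat + 4 × carbohydrate.

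- ORAL IMPACT: 4 × 16.7 + 9 × 8.3 + 4 × 40.2 = 66.8 + 74.7 + 160.8 = 302.3 kcal. The shares are 22.1, 24.7 and 53.2%.
- Control: 4 × 13 + 9 × 8.3 + 4 × 43.94 = 52.0 + 74.7 + 175.76 = 302.46 kcal. The shares are 17.2, 24.7 and 58.1%.

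Both totals agree closely with the printed 302.8, and both sets of shares round to the printed splits. Isocaloric is confirmed. The protein, carbohydrate, energy and energy-share rows all agree, so a misprint in one cell or damage in text extraction is unlikely.

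**3. Does isonitrogenous hold?** No conversion factor is needed for the direction. Casein/whey is equal in the two products, and arginine and RNA, both of which contain nitrogen, occur only in ORAL IMPACT. Its nitrogen content must be higher.

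**4. How large is the gap?** On label protein, 16.7 / 13.0 = 1.28, or 28% more. By component, the nitrogen contents below are assumptions, because the article gives none.

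| Assumption | Control N (g) | ORAL IMPACT N (g) | Ratio |
|---|---|---|---|
| Label protein / 6.25 | 2.08 | 2.67 | 1.28 |
| Casein/whey 16% N; arginine 32.2% N | 13 × 0.16 = 2.08 | 2.08 + 3.74 × 0.322 = 3.28 | 1.58 |
| Casein/whey / 6.38; arginine 32.2% N | 2.04 | 3.24 | 1.59 |
| As the two rows above, plus RNA at 15–17% N | 2.04–2.08 | 3.30–3.35 | 1.61–1.62 |

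The arginine share is 4 × 14.007 / 174.2 = 0.322, from its molecular formula. The label figure understates the nitrogen gap because a gram of arginine carries about twice the nitrogen of a gram of casein/whey. By component, the gap is about 1.2 g nitrogen per sachet, at one sachet a day.

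**5. Is the sample size touched?** No. With a difference of 0.1% per day, an SD of 0.21% per day, two-sided 0.05 and 80% power, the normal formula gives 69.2, so 70 per group. The t-test version gives 70.2, so 71, as the article states. None of these inputs depends on the composition of the control.

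**The case against.** The strongest reply is that the nitrogen gap is not a separate confounder. All of the extra protein is arginine, which the article names as one of the three ingredients under test, and which it expects to improve nitrogen balance. Under 1:1 randomisation, a MAMA difference is an effect of the ORAL IMPACT package against an isocaloric control. This stands. A reader might infer from Table 2 that an effect on MAMA could not be attributed to immunonutrition at all. The documents do not support that, because the extra nitrogen comes from the tested ingredients. Only the division of the effect by mechanism is out of reach.

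A second reply is that the sentence is hedged background, and that the primary objective (Objectives and endpoints) asks for safety, efficacy, nutritional status and quality of life, not mechanism. That is fair and limits the weight of the point. It does not make the description of the comparator true.

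A third reply is that the gap is small. The Discussion cites a requirement of 1.2 g/kg protein daily. At an assumed 50 to 80 kg this is 60 to 96 g, so 3.7 g is about 4 to 6% of it. Expressed as protein, 1.2 g nitrogen is 1.2 × 6.25 = 7.5 g, or about 8 to 12%, but that conversion treats nitrogen from one free amino acid as if it were whole protein. The documents give no basis for saying that such an amount would move MAMA, and none for ruling it out.

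A reader might also take issue with the trial being called placebo-controlled, or with the control's higher linoleic acid content. The first is loose terminology: the same sentence also speaks of a control supplement. The second contradicts nothing, since total fat is 8.3 g in both and fat without ω-3 must be something else.

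**Conclusion.** The Trial Rationale misstates a property of the comparator. By Table 2 the control is isocaloric but not isonitrogenous. ORAL IMPACT has 28% more protein per sachet on the label, and about 58 to 62% more nitrogen by component (about 3.3 against 2.1 g). The direction follows from Table 2 whatever conversion is used; the component figures rest on the assumed nitrogen contents.

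The consequence is limited. The between-arm comparison, the sample size and the attribution of a MAMA effect to the immunonutrient package are unaffected. What this contrast cannot settle on MAMA is the exact role of immunonutrition or the immune-modulation hypothesis in the Conclusion, because added amino-acid nitrogen remains a competing explanation. This should be corrected, but it is not a reason to doubt the trial's main comparison.

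**What to change.** Verify Table 2 with the manufacturer and reconcile it with the Trial Rationale, correcting whichever is wrong. If Table 2 stands:

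- delete isonitrogenous from the Trial Rationale;
- state the nitrogen content of each sachet, since protein grams alone understate the difference;
- limit the conclusion to ORAL IMPACT against an isocaloric, lower-nitrogen control, in both the Trial Rationale and the Conclusion, with no claim that a nutritional (nitrogen) effect has been excluded.

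An analysis of MAMA adjusted for baseline dietary protein would not rescue the mechanistic claim and need not be added. The nitrogen gap arises after baseline, from the assigned sachet, and is fully aliased with arm.

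The cost is one check with the manufacturer and a few sentences of wording. The mechanistic claim becomes narrower. No endpoint, sample size or power figure changes.

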## Methods/Design

### Subject recruitment

After the positive vote of the ethics committee of the Faculty of Medicine, Ruprecht-Karls University of Heidelberg, enrollment of 142 newly registered patients for primary LT will be started early in September 2007 in this prospective multicenter placebo-controlled randomized double-blind clinical trial with two parallel treatment groups receiving either study product or control supplement. Patients are considered for recruitment to the study according to inclusion and exclusion criteria (Table 1). Each subject is expected to be recruited on the day of registration on the waiting list for LT. Study nutrition ends on the day of transplantation. To assess early outcome after transplantation patients are followed for 12 postoperative weeks. The duration of the overall trial is expected to last approximately 36 months. The actual duration of trial may vary due to the availability of patients meeting the criteria after registration for LT.

**Table 1 T1:** Criteria for inclusion and exclusion of patients.

**Inclusion criteria**	**Exclusion criteria**
patients meeting all of the following criteria are considered for inclusion in the study: - men and women, 18–68 years of age - scheduled for first liver transplantation - written informed consent - protein-calorie malnutrition defined as mid-arm muscle area (MAMA) <85% standard	patients with any of the following will not be included in the trial: - patients <18 and >68 years - pregnant or nursing women - history of hypersensitivity to arginine, ω-3 fatty acids, or nucleotides - inability to take oral nutrition - patients with fulminant or subacute hepatic failure - mental condition rendering the subject incapable of understanding the nature, scope, and consequences of the trial No subject will be enrolled in this study more than once.

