### Sample size calculation

The sample size calculation is based on the detection of significant differences in MAMA, one of the primary endpoint parameters of this trial. A clinical trial on enteral hyperalimentation in malnourished patients with cirrhosis and ascites [26] was used as an exemplary model. The rate was measured in percent per day, i.e. MAMA changes divided by number of days between admission and discharge. After eliminating the gross outlier of this study, the standard deviation of this rate was 0.21% per day. The clinically relevant difference was set to 0.1% MAMA per day. Therefore, the sample size necessary for the trial with a power of 80% and a two-sided significance level of 0.05 was calculated to be 71 patients per group. An assumed 10% drop-out rate in this trial (due to non-compliance, intolerance, premature discontinuation, etc) will raise the sample size to 78 patients per group. Therefore, at least a total of 156 patients have to be included to the trial in order to yield 142 completers.

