### Randomization and treatment

Randomization (1:1) will be performed by the algorithm programmed in specific computer software and a randomization list will be prepared. The randomization list will be prepared by the institution that is responsible for the packaging of the study and control products and kept in safe and confidential custody at this institution. Both study product and control product will be of same form and appearance (powder) including the packaging material. If it is medically imperative to know which product the patient consumes, emergency envelopes contain the information on the subject's study product.

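### The abstract and the recruitment section set enrolment at 142, but the sample-size section makes 142 the number of completers and requires at least 156 included

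*Protocol article*

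**What the plan says.** Three places in the protocol article give a trial size.

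- Abstract, Methods/design: the trial has "two parallel groups comprising a total of 142 newly registered patients for primary liver transplantation".
- Subject recruitment: the plan is "enrollment of 142 newly registered patients for primary LT will be started early in September 2007". The same section has each patient recruited on the day of listing, so this counts patients at entry.
- Sample size calculation: the number needed "with a power of 80% and a two-sided significance level of 0.05 was calculated to be 71 patients per group". A 10% drop-out allowance "will raise the sample size to 78 patients per group", and the section concludes that "at least a total of 156 patients have to be included to the trial in order to yield 142 completers".

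Two other places affect how the figures are read. Trial design and schedule defines a completer by intake: at least 80% of the prescribed calories over the preoperative period. Statistics and data management makes intent-to-treat the basis of all analyses, with per-protocol and completer analyses as additions.

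**The concern.** The same number, 142, stands for patients entering the trial in the abstract and recruitment section, and for patients completing it in the sample-size section. Patients counted on the day of listing cannot already be completers, so the two uses cannot both hold. The sample-size section also words 156 as a minimum, and the other two places fall 14 short of it.

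The enrolment total decides when recruitment stops, and the calculation has almost no slack at 71 per group. It also affects the single interim analysis, which is triggered when half of the patients have finished: half of 142 is 71 and half of 156 is 78, and the text does not say which total applies.

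**Working it through.** **Inputs**, all from the protocol article:

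- SD: "the standard deviation of this rate was 0.21% per day".
- Difference: "The clinically relevant difference was set to 0.1% MAMA per day".
- Two-sided 5% level, 80% power, 10% drop-out (Sample size calculation).
- Equal allocation: "Randomization (1:1) will be performed by the algorithm programmed in specific computer software".

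**1. Reproducing 71 per group.** The standardised difference is 0.1/0.21 = 0.476. The normal approximation gives n = 2 × (1.960 + 0.842)² × (0.21/0.1)² = 69.2, so 70 per group. The two-sample t-test, using the noncentral t distribution with noncentrality 0.1/(0.21 × √(2/n)) and 2n − 2 degrees of freedom, gives 79.9% at 70 and 80.4% at 71. The stated 71 per group, 142 in total, reproduces exactly as the number of patients contributing data.

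**2. Reproducing 78 per group.** 71 × 1.10 = 78.1, which matches the stated 78 and the total of 156.

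**3. If 142 are enrolled.** With 10% lost, 142 × 0.90 = 127.8 remain, or 63.9 per group. If all 142 are analysed, there are 71 per group.

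**4. If 156 are enrolled.** 156 × 0.90 = 140.4 remain, or 70.2 per group. That is 1.6 fewer than 142. The loss at which 156 would yield 142 is 1 − 142/156 = 9.0%.

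**5. Inflation by division.** 71/0.90 = 78.9, so 79 per group and 158 in total. 158 × 0.90 = 142.2.

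| Enrolled | Analysed | Per group | Power, t-test | Power, normal approximation |
|---|---|---|---|---|
| 142, 10% contribute no data | 127.8 | 63.9 | 76.1% | 76.8% |
| 142, all analysed | 142 | 71 | 80.4% | 81.0% |
| 156, 10% contribute no data | 140.4 | 70.2 | 80.0% | 80.5% |

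**The case against.** The strongest defence is that the 76% is a worst case. It requires recruitment to stop at 142 despite the sample-size section, and every drop-out to be missing from the analysis. The second condition is not given. Intent-to-treat is the main basis, and a completer is defined by calories consumed, not by having outcome data. Patients who count as drop-outs through poor compliance or intolerance may still have monthly mid-arm muscle area measurements and be analysed. This stands: 76% is a lower bound on nominal power at the planned effect, and 80.4% is the upper bound if nobody is lost. Non-adherence could also dilute the effect itself, but the article gives no figure from which to size that.

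The defence does not remove the contradiction. If 142 enrolled is enough because everyone is analysed, then the sample-size section is wrong to require 156. One of the texts has to change either way.

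A second defence is that the reader can work out what happened: the sample-size section alone derives the number and says plainly what 142 means, so the other two places probably omit the drop-out allowance. That is plausible and points to the simplest repair, but the article does not say so.

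A reader might also infer that 156 is too small, since it yields 140 completers. The figures do not support any loss of power there. The gap is under two patients, power stays at 80.0%, and 156 is stated as a minimum, which already permits 158.

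**Conclusion.** The contradiction holds and should be corrected: 142 is the enrolment figure in the abstract and recruitment section, and the completer figure in the sample-size section, where at least 156 must be included. The shortfall in the first two places is 14 patients.

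If 142 are enrolled, nominal power lies between about 76% (drop-outs contribute no data) and 80.4% (all analysed). This takes as given the plan's difference of 0.1% per day, SD of 0.21% per day, two-sided 5% t-test and 10% drop-out. It would go too far to say that the trial certainly loses its 80% power, because the article does not settle whether drop-outs are analysed.

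Multiplying by 1.10 instead of dividing by 0.90 is a minor slip. It makes the promise of 142 completers inexact by 1.6 patients and has no material effect on power.

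**What to change.** In the abstract and in Subject recruitment, replace 142 by the enrolment target of the sample-size section (at least 156), and describe 142 as the number of completers. This is a wording change in two places and adds no patients beyond what the sample-size section already requires.

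If the sponsor really intends to enrol only 142, correct the sample-size section instead, and restate the power as about 76% under its own 10% loss assumption. The cost is a lower stated power.

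While that section is open, make its last sentence agree with its inputs: either keep 156 and state about 140 completers, or use 79 per group and 158 in total, which is two patients more. Either is acceptable, since power is 80.0% at 156. The chosen total should also be the one whose half triggers the interim analysis.
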